## Abstract

**Background:**

Postoperative atrial fibrillation (PoAF) after cardiac surgery has a high incidence of 30%, but its management is controversial. Two strategies are recommended without evidence of a superiority of one against the other: rate control with beta-blocker or rhythm control with amiodarone. Landiolol is a new-generation beta-blocker with fast onset and short half-life. One retrospective, single-center study compared landiolol to amiodarone for PoAF after cardiac surgery with a better hemodynamic stability and a higher rate of reduction to sinus rhythm with landiolol, justifying the need for a multicenter randomized controlled trial. Our aim is to compare landiolol to amiodarone in the setting of PoAF after cardiac surgery with the hypothesis of a higher rate of reduction to sinus rhythm with landiolol during the 48 h after the first episode of POAF.

**Methods:**

The FAAC trial is a multicenter single-blind two parallel-arm randomized study, which planned to include 350 patients with a first episode of PoAF following cardiac surgery. The duration of the study is 2 years. The patients are randomized in two arms: a landiolol group and an amiodarone group.

Randomization (Ennov Clinical®) is performed by the anesthesiologist in charge of the patient if PoAF is persistent for at least 30 min after correction of hypovolemia, dyskalemia, and absence of pericardial effusion on a transthoracic echocardiography done at bedside.

Our hypothesis is an increase of the percentage of patients in sinus rhythm from 70 to 85% with landiolol in less than 48 h after onset of PoAF (alpha risk = 5%, power = 90%, bilateral test).

**Discussion:**

The FAAC trial was approved by the Ethics Committee of EST III with approval number 19.05.08. The FAAC trial is the first randomized controlled trial comparing landiolol to amiodarone for PoAF after cardiac surgery. In case of higher rate of reduction with landiolol, this beta-blocker could be the drug of choice used in this context as to reduce the need for anticoagulant therapy and reduce the risk of complications of anticoagulant therapy for patients with a first episode of postoperative atrial fibrillation after cardiac surgery.

**Trial registration:**

ClinicalTrials.gov NCT04223739. Registered on January 10, 2020.

**Supplementary Information:**

The online version contains supplementary material available at 10.1186/s13063-023-07353-6.

## Introduction

### Background and rationale {6a}

Postoperative atrial fibrillation (PoAF), defined as new-onset atrial fibrillation in the immediate postoperative period, is a clinically relevant problem occurring in 20 to 50% of patients after cardiac surgery [1]. Intra- and postoperative changes affecting atrial fibrillation triggers and pre-existing atrial substrate may increase atrial vulnerability to arrhythmia. PoAF has been associated with hemodynamic instability, prolonged hospital stays, infections, renal complications, bleeding, increased in-hospital death, and greater healthcare costs, and it has been shown to be a risk factor for stroke [1]. However, its management is controversial. Two therapeutic strategies are recommended without evidence of a superiority of one against the other [1–3]: the rate control with negative chronotropic agents as beta-blockers or rhythm control with amiodarone as an anti-arrhythmic agent. A study by Gillinov et al. showed no difference in complications and duration of hospital stay between these two strategies [4]. However, this study suffered from some limitations as the modality of beta-blocker use (oral route, no predetermined administration plan, goal heart rate of 100/min which is still high concerning myocardial energy balance) [5]. Landiolol is a new generation of intra-venous beta-blocker with fast onset (1 min) and short half-life (4 min). Landiolol has been used for over 20 years in Japan [6], and its use has recently been approved in Europa for perioperative supraventricular arrhythmia. Due to its S-Enantiomer conformation, landiolol has less of a negative inotropic effect than esmolol (only other available intravenous beta-blocker) [7]. One study compared landiolol to amiodarone for PoAF after cardiac surgery with a better hemodynamic stability (less bradycardia and hypotension) and a higher rate of reduction to sinus rhythm with landiolol [8]. However, this was a retrospective, single-center study including few patients [8].

In this protocol, we describe the design of a multicenter randomized controlled trial to compare landiolol to amiodarone for the treatment of new-onset PoAF after cardiac surgery.

### Objectives {7}

The primary objective is the number of patients in sinus rhythm 48 h after the first episode of POAF after cardiac surgery. The secondary objectives are the hemodynamic tolerance, the ICU and hospital length of stay, and the recurrence of POAF and/or thromboembolic complications and/or hemorrhagic complications and/or number of patients with an adverse event due to landiolol or amiodarone, within 2 months and 1 year after surgery. Table 1 summarizes the objectives and time points.

**Table 1 Tab1:** Objectives

	Outcomes	Measurements	Time points
Primary	Proportion of patient in sinus rhythm at 48 h	Number (percentage) of patients	48 h
Secondary	Hemodynamic tolerance of treatment	Incidence of MAP < 60 mmHg and/or bradycardia as heart rate < 40/min	ICU LOS
	ICU LOS	Total days	ICU LOS
	Hospital LOS	Total days	Hospital LOS
	Recurrence of PoAF	EKG	2 months and 1 year
	Thromboembolic complications	Stroke or embolic ischemia	2 months and 1 year
	Hemorrhagic complications	Active bleeding uncontrollable, with hemodynamic instability, with an urgency treatment, or in a location with functional or vital prognosis	2 months and 1 year
	Adverse events to amiodarone or beta-blockers		2 months and 1 year

*EKG* Electrocardiogram, *ICU* Intensive care unit, *LOS* Length of stay, *MAP* Mean arterial pressure

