#### Secondary outcomes

The secondary outcomes are hemodynamic stability (hypotension, bradycardia), duration of stay in the ICU and in the hospital, number of patients (in percentage, 95% CI) with a recurrence of PoAF within 2 months and 1 year after surgery, number of patients (in percentage, 95% CI) with a thromboembolic complication within 2 months and 1 year after surgery, number of patients (in percentage, 95% CI) with a hemorrhagic complication within 2 months and 1 year after surgery, and number of patients (in percentage, 95% CI) with an adverse event due to landiolol or amiodarone within 2 months and 1 year after surgery.

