### Concealment mechanism {16b}

There is no blinding in this open-label study (care providers know the group allocation, but the patient and the surgeon are not aware of the group allocation).

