## Assignment of interventions: blinding

### Who will be blinded {17a}

Patients are blinded of the study group. Care providers are aware of the group allocation.

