## Data collection and management

### Plans for assessment and collection of outcomes {18a}

Data, patients’ consent, and outcomes will be recorded by the care provider in charge of the patient and a dedicated local research coordinator before and after enrollment using eCRFs (Ennov Clinical®).

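### One secondary outcome counts only adverse events attributed to the study drug, and the attribution appears to be made unblinded, so that comparison can reflect opinion rather than harm

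*Protocol article*

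**What the plan says.** The Objectives section {7} includes the "number of patients with an adverse event due to landiolol or amiodarone" among the secondary objectives. The Secondary outcomes section repeats the attribution and gives the time points: patients "with an adverse event due to landiolol or amiodarone within 2 months and 1 year after surgery". Table 1 has a matching row, "Adverse events to amiodarone or beta-blockers", whose measurement cell is empty.

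On who sees and records events:
- Section 18a: "outcomes will be recorded by the care provider in charge of the patient and a dedicated local research coordinator".
- Section 17a: "Care providers are aware of the group allocation".
- Section 16b: "care providers know the group allocation, but the patient and the surgeon are not aware of the group allocation".
- Oversight and monitoring: no committee is planned, and section 21a adds that there is no safety board.

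Section 20a assigns categorical secondary outcomes to a chi-square or Fisher exact test, with two-sided significance at 0.05.

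**The concern.** Randomisation makes the arms comparable for all events that occur. It does not do so for the subset that someone, knowing the treatment, later decides the drug caused. If clinicians expect a given side effect from one drug more than from the other, the same event can be counted in one arm and put down to the operation in the other.

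The protocol itself gives grounds for differing expectations. Its Background cites a retrospective study with better hemodynamic stability on landiolol, and its Discussion looks for excellent hemodynamic tolerance in a beta-blocker.

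At stake is one tested secondary outcome. It matters somewhat more than its rank suggests, because it is the only listed outcome for other drug toxicity out to 1 year: in Table 1, hemodynamic tolerance is followed only for the ICU stay.

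**Working it through.** **1. The plan's own figure.** The only design calculation is 159 per arm for 70% against 85%, two-sided 5%, power 90%. The unpooled normal formula gives

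n = (1.960 + 1.282)² × (0.70×0.30 + 0.85×0.15) / 0.15² = 157.6, so 158 per arm.

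The pooled-variance version gives 161. The stated 159 is reproduced to within 2 patients, and this point does not touch it. The planned 175 per arm is used below.

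**2. Is there an attribution filter, and who applies it?** The Objectives text and the Secondary outcomes section both use causal wording, so a filter is part of the definition. No section names the person who judges causality. The only people named as blinded are the patient and, in section 16b, the surgeon, and section 18a gives neither a role in recording outcomes. Of the two roles it does name, one is unblinded and the other's status is not stated. With no committee planned, no blinded assessor is described. Unblinded attribution is therefore a sound inference, but not a stated fact.

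**3. Effect on the test.** Let r be the true proportion of patients with an event, equal in both arms, and let s₁ and s₂ be the shares attributed to the drug in the two arms. The counted proportions are r·s₁ and r·s₂. For example, r = 20% with shares of 80% and 50% gives 0.20×0.80 = 16% against 0.20×0.50 = 10%. The probability of p < 0.05 was found by exact enumeration of two binomial counts with n = 175 each, using the two-sided chi-square test without continuity correction. With equal shares it is about 5%.

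The documents give neither r nor the shares, so every row is an assumption.

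| Shares attributed | True rate, both arms | Counted rates | False-positive rate |
|---|---|---|---|
| 60% v 50% | 10% | 6% v 5% | 6.7% |
| 60% v 50% | 20% | 12% v 10% | 9.1% |
| 70% v 50% | 5% | 3.5% v 2.5% | 7.8% |
| 70% v 50% | 20% | 14% v 10% | 21.0% |
| 80% v 50% | 5% | 4% v 2.5% | 11.7% |
| 80% v 50% | 10% | 8% v 5% | 20.1% |
| 80% v 50% | 20% | 16% v 10% | 38.9% |
| 80% v 50% | 30% | 24% v 15% | 57.1% |

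**4. Masking.** Suppose the true rates are 25% and 15%. With every event counted, power is 65.4%. If 50% of events are attributed in the first arm and 80% in the second, the counted rates are 0.25×0.50 = 12.5% and 0.15×0.80 = 12.0%, and the chance of a significant result falls to 5.2%. This example was chosen so that the shares nearly cancel the excess. It shows that masking is possible, not that it is likely.

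**The case against.** **The person who attributes events is not named.** This is correct. A reader might infer that the protocol hands the causal judgement to the care provider. Section 18a says only who records outcomes, and it names the coordinator as well. A cardiology consultation at 2 months also evaluates the treatment, and the text does not say whether events are attributed there. The point must rest on an inference, as it does here.

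**The wording may be shorthand for a list of known effects.** The Table 1 row could mean known effects of the two drug classes, ticked alike in both arms, with the list held in the full protocol or eCRF. That is possible, and the absence of such a list from an article is not the criticism. But Table 1 does not remove the causal wording that stands in both the Objectives text and the Secondary outcomes section. If the eCRF captures only attributed events, no analysis plan could later recover the others.

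**Other safety outcomes are unaffected.** This stands. A reader might infer that the trial's safety comparison as a whole is unreliable. Hypotension and bradycardia, thromboembolic complications and hemorrhagic complications are separate outcomes defined without attribution.

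**The sizes are assumed.** This also stands. The larger figures need a 30-point gap and fairly common events. With a 10-point gap the excess over 5% is small.

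**All-cause counting has its own costs.** After cardiac surgery many events are surgical and dilute a drug effect, and unblinded staff would still decide what is recorded. That limits the gain but does not justify testing the attributed subset.

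**Conclusion.** The point holds for one secondary outcome. As defined, it lets an opinion formed after randomisation, apparently with the arm known, select which events count, and the result is then tested at 0.05. The primary outcome, the sample size and the other safety outcomes are not affected.

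The size cannot be calculated from the documents. The ranges shown run from barely above the nominal 5% to more than ten times it (57.1 / 5 ≈ 11), depending wholly on the assumed event rate and attribution gap. The upper end should not be read as an expected value, nor the masking example as a prediction.

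The conclusion rests on two things: that the causal wording is applied as written, and that no blinded assessor exists beyond what the article describes. This is a cheap improvement, between one to consider and one that should be made.

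**What to change.** In the Objectives text, in Table 1 (including its empty measurement cell) and in the Secondary outcomes section, redefine the outcome as the number of patients with any event from one prespecified list. The list should be the same in both arms and recorded the same way in both, regardless of presumed cause. Make that the tested comparison. Report events judged drug-related descriptively by arm, without a test.

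The cost is a wording change and an eCRF item completed for every listed event rather than only for attributed ones. The drawbacks are slightly more data entry, some dilution of a drug effect by background surgical events, and ascertainment that remains unblinded. Objective criteria for each listed event would reduce the last of these but not remove it.

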### Trial design {8}

The FAAC trial is a multicenter, prospective, randomized, controlled, single-blinded, two-arm study comparing landiolol to amiodarone for the treatment of atrial fibrillation following cardiac surgery. The FAAC trial was approved by the Ethics Committee of EST III with approval number 19.05.08 (registration number ID RDB: 2019-A00763-54). The FAAC trial is conducted in accordance with the Declaration of Helsinki, and the French laws [9]. The privacy of the participants and their personal medical records will be guaranteed by treating the data according to the French law n. 78–17 of 6 January 1978 and the European Union Data Protection Directive (95/46/EC24 October 1995).

A checklist of recommended items to address in a clinical trial protocol according to the Standard Protocol Items: Recommendations for Interventional Trials (SPIRIT 2013 Checklist) is provided in Additional file 1.

The approved initial version of FAAC is v2 14 05 2019 (ongoing version v5 28.09.2021); the recruitment began in January 2020. The estimated end of the study will be December 2024. Participants are currently being recruited and enrolled. The sponsor (CHU de Caen) is responsible for reporting any protocol modifications to the centers, to the ethic committees, and to the French Agency of Drug and Medication (ANSM).

## Methods: participants, interventions, and outcomes

### Study setting {9}

Patients are recruited in eleven French institutions (details in Additional file 2). The study sponsor is the Research and Innovation Department of the University Hospital of Caen, a public academic institution in France.

### Eligibility criteria {10}

Patients scheduled for cardiac surgery are eligible for the study.

Inclusion criteria are:Adult patients hospitalized in the cardiac intensive care unit after cardiac surgery including coronary artery bypass and/or aortic valve repair and/or ascending aorta surgery;New onset of postoperative atrial fibrillation persistent more than 30 min;Patient with a social security number;Patient with written informed consent.

Exclusion criteria are:Patients with hemodynamic instability with the need of an electrical cardioversion;Preoperative treatment with anticoagulant therapy;Contra-indication to amiodarone or beta-blockers;Sepsis;Slow PoAF (heart rate < 90/min);Patient with inotropic support;Patient history of atrial fibrillation;Emergency surgery, ventricular assist device, heart transplantation, TAVR, mechanical valve, mitral valve, or tricuspid valve repair.

### Who will take informed consent? {26a}

Patients are screened and informed during the consultation before surgery (conducted in France by the anesthesiologist, which is also the intensivist for the postoperative care), and they are screened and re-informed by the intensivist if POAF occur in the postoperative period and included after providing written consent. According to the French laws, only medical doctors recorded as investigators in the present study can inform and obtain written informed consent [9]. They should have validated an international council for harmonization for Good Clinical Practices and follow a specified formation for the study design of the FAAC study performed in initiation site meeting.

### Additional consent provisions for collection and use of participant data and biological specimens {26b}

Not applicable.

## Interventions

### Explanation for the choice of comparators {6b}

The FAAC trial will compare amiodarone and beta-blockers, which are the two most used therapeutics at bedside and largely recommended by learning societies [2, 3]. The landiolol was chosen as a beta-blocker because of its easy intravenous use, short delay of action, and rapid elimination.

### Intervention description {11a}

Patients who underwent cardiac surgery and have a de novo persistent POAF (for at least 30 min) in the cardiac intensive care unit (ICU) and are eligible for the study are randomized after informed consent, after exclusion of hypovolemia and pericardial effusion with a transthoracic echocardiography and after exclusion of dyskalemia or anemia with an arterial blood gas performed in routine care. Randomization is performed by the anesthesiologist in charge of the patient in the cardiac ICU using CSOnline website (Ennov, Paris, France), 24/7 available. The randomization sequence is generated by the statistician of the study using permutated blocks and stratified by center. Patients are randomized in either the landiolol group or the amiodarone group (Fig. 1).

**Fig. 1 Fig1:**
[figure not shown]
Flowchart of the FAAC study

In the landiolol group (Fig. 2), landiolol is administered intravenously without bolus at a starting dose of 2.5 μg/kg/min. This dose is increased by steps of 2.5 μg/kg/min every 10 min until a maximum dose of 80 μg/kg/min in order to reach a target heart rate (HR) of less than 90 beats per minute (bpm) [6]. Once this target heart rate is achieved, beta-blocker therapy is bridged within 24 h of landiolol infusion with bisoprolol 1.25 mg twice daily if the maximum dose of landiolol was inferior to 15 μg/kg/min or bisoprolol 2.5 mg twice daily if the maximum dose of landiolol was superior to 15 μg/kg/min (Additional file 3). Landiolol infusion is then discontinued.

**Fig. 2 Fig2:**
[figure not shown]
Landiolol group algorithm. IV, intravenous; PoAF, postoperative atrial fibrillation

In the amiodarone group (Fig. 3), amiodarone is administered intravenously with a bolus of 5–7 mg/kg over 1 h and a subsequent continuous infusion of 1.0 g per day until reduction to sinus rhythm [3]. If reduction to sinus rhythm occurs or if the target heart rate drops below 90 beats per minute, intravenous infusion of amiodarone is discontinued and bridged via oral route with 200 mg amiodarone daily.

**Fig. 3 Fig3:**
[figure not shown]
Amiodarone group algorithm. IV, intravenous; PoAF, postoperative atrial fibrillation

For both groups, the curative anticoagulation is started if PoAF is > 48 h and the CHA_2_DS_2_-VASc score is ≥ 1 (for men) or ≥ 2 (for women) [10]; the treatment (bisoprolol or amiodarone) is continued for 2 months, until cardiology consultation for evaluating the treatment and the anti-coagulation prescription [11].

### Criteria for discontinuing or modifying allocated interventions {11b}

Criteria for discontinuing the allocated treatment are extreme bradycardia (defined as heart rate < 40/min), arterial hypotension with MAP < 60 mmHg, or allergy with graduate 3 or 4 conducting to epinephrine use.

### Strategies to improve adherence to interventions {11c}

Patients are hospitalized, and therapeutics will be administered intravenously by nurses explaining that the attempt adherence will be excellent.

### Relevant concomitant care permitted or prohibited during the trial {11d}

All concomitant care and interventions are permitted during the trial. All patients have a continuous EKG, SpO_2_, and blood pressure monitoring during the intravenous treatment (amiodarone or landiolol). Usual care for postoperative cardiac surgery will be continued.

### Provisions for post-trial care {30}

No provisions are provided, because no ancillary and post-trial care is designed. Usual care will be conducted in the post-trial period.

The sponsor has insurance in accordance with the legal requirements in France. This insurance provides coverage for damage to research subjects through injury or death caused by the study. The insurance applies to the damage that becomes apparent during the study or within 10 years after the end of the study.

### Outcomes {12}

#### Primary outcome

The primary outcome is the number of patients (in percentage, 95% CI) in sinus rhythm 48 h after the first episode of PoAF after cardiac surgery. This primary outcome was chosen to compare the efficacy of both landiolol and amiodarone to reduce PoAF in the first 48 h which is the delay recommended to start the anticoagulation if PoAF is not reduced [3].

#### Secondary outcomes

The secondary outcomes are hemodynamic stability (hypotension, bradycardia), duration of stay in the ICU and in the hospital, number of patients (in percentage, 95% CI) with a recurrence of PoAF within 2 months and 1 year after surgery, number of patients (in percentage, 95% CI) with a thromboembolic complication within 2 months and 1 year after surgery, number of patients (in percentage, 95% CI) with a hemorrhagic complication within 2 months and 1 year after surgery, and number of patients (in percentage, 95% CI) with an adverse event due to landiolol or amiodarone within 2 months and 1 year after surgery.

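### Bleeding and thromboembolic events are counted from surgery, before randomisation, and hemodynamic intolerance is counted over the ICU stay, which is itself an outcome

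*Protocol article*

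**What the plan says.** Secondary outcomes, under Outcomes {12}, gives four event outcomes the same clock. Patients are counted "with a recurrence of PoAF within 2 months and 1 year after surgery", "with a thromboembolic complication within 2 months and 1 year after surgery", "with a hemorrhagic complication within 2 months and 1 year after surgery" and "with an adverse event due to landiolol or amiodarone within 2 months and 1 year after surgery". Objectives {7} repeats the clock: "within 2 months and 1 year after surgery".

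For hemodynamic tolerance, Table 1 gives the measure as "Incidence of MAP < 60 mmHg and/or bradycardia as heart rate < 40/min" and enters ICU length of stay as the time point. ICU and hospital stay are secondary outcomes in their own right, measured in total days.

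Randomisation is later than surgery. Under Intervention description {11a}, patients must first "have a de novo persistent POAF (for at least 30 min) in the cardiac intensive care unit", then pass an echocardiography and blood gas check and give consent. Implementation {16c} places randomisation in the cardiac ICU. The primary outcome, by contrast, is timed from the first episode of atrial fibrillation.

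Statistical methods {20a} compares categorical secondary outcomes by chi-square or Fisher test, that is, as simple proportions without person-time. No section limits secondary events to those after randomisation.

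**The concern.** There are two separate problems, and they affect different outcomes.

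- **Pre-randomisation events.** A serious bleed or stroke between surgery and randomisation meets the stated definition, although neither drug, nor the anticoagulation decision that follows from persistent fibrillation, could have caused it. The abstract's Discussion justifies the trial partly by fewer complications of anticoagulant therapy, so a blunted bleeding comparison weakens one of its own arguments.
- **A window that treatment may change.** If one drug shortens the ICU stay, its patients have less time in which to record a low pressure or slow heart rate. The link can also run the other way, because hypotension can prolong a stay. Hemodynamic stability is part of the stated rationale for landiolol in the Background. If the ICU stay is read as the whole stay, pre-treatment hypotension is counted as well.

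**Working it through.** **The plan's own figure.** Sample size {14} needs 159 per arm for 70% vs 85% (two-sided 5%, power 90%). The pooled two-proportion formula gives 161 per arm and the unpooled one 158, so the figure reproduces. At the planned 175 per arm, power for the primary outcome is 92.3%. None of this depends on the secondary windows.

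**Inputs for the illustrations.** From the document: 175 per arm, two-sided 5%, comparison of proportions. Assumed, because the document gives no secondary event rates, ICU stay or interval from surgery to fibrillation: every rate and stay below.

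**Formula.** Power = Φ[(|p2 − p1| − 1.96·SE0)/SE1], with SE0 = √(2·p̄(1 − p̄)/n), p̄ the mean of p1 and p2, and SE1 = √([p1(1 − p1) + p2(1 − p2)]/n).

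**(a) Events counted from surgery.** Let a share q of each arm have an event before randomisation. A true later rate p is then observed as q + (1 − q)p. With true rates of 5% and 12%:

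| q | Observed rates | Risk ratio | Power |
|---|---|---|---|
| 0% | 5.0% vs 12.0% | 2.40 | 65% |
| 2% | 6.9% vs 13.8% | 1.99 | 56% |
| 5% | 9.8% vs 16.4% | 1.68 | 45% |
| 10% | 14.5% vs 20.8% | 1.43 | 34% |

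First row in full: p̄ = 0.085, SE0 = 0.0298, SE1 = 0.0296, so (0.070 − 0.0584)/0.0296 = 0.39 and Φ(0.39) = 0.65. The risk difference shrinks only by the factor 1 − q (from 7.0 to 6.3 points at q = 10%). Most of the power loss comes from the added variance. When the drugs do not differ, both observed rates are equal, so the type I error stays nominal.

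**(b) Intolerance counted over the ICU stay.** With the same daily risk r in both arms and a stay of d days, the chance of at least one event is 1 − (1 − r)^d. For 3 vs 4 days:

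| r per day | Proportion with an event | Chance of p < 0.05 |
|---|---|---|
| 5% | 14.3% vs 18.6% | 19% |
| 10% | 27.1% vs 34.4% | 31% |
| 15% | 38.6% vs 47.8% | 41% |
| 20% | 48.8% vs 59.0% | 48% |

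The drugs have no effect on daily risk here, so the last column should be 5%. Using a constant hazard of 0.05 to 0.20 per day, 1 − exp(−hd), gives 19 to 46%. With equal stays, or a common fixed window, the excess disappears.

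**(c) Outcomes that pre-randomisation events cannot reach.** A recurrence cannot come before the first episode, and an event due to a study drug cannot come before that drug. For these two the surgery clock only shortens follow-up: an assumed lag of 2 to 5 days is 3 to 8% of 60 days (2/60, 5/60) and 0.5 to 1.4% of a year (2/365, 5/365).

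**The case against.** The strongest reply has four parts.

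- **Few early events may qualify.** Hypovolemia, anemia and pericardial effusion are ruled out before randomisation, patients on inotropes are excluded, consent is needed, and the bleeding definition is severe. This limits q, but a bleed that was treated and resolved could still be counted, and an earlier bleed or stroke is not an exclusion.
- **Randomisation balances what came before.** This stands. For bleeding and thromboembolism the cost is dilution, not bias. For length of stay, pre-randomisation days leave the expected difference in means unchanged and only add variance.
- **The ICU stay may not differ.** The Background cites a trial of rate versus rhythm control with no difference in hospital stay. That trial used an oral beta-blocker, and hospital stay is not ICU stay, but the bias is indeed conditional on a difference that the documents do not predict.
- **The article is condensed.** The detailed schedule is in Additional file 4, and calling the outcome tolerance of treatment suggests a start at treatment. But the article does not leave the start point open for the events: it states surgery, twice. For tolerance, the label does not fix the start and Table 1 ties the period to the stay.

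A reader might go further and infer that observation time differs by design, because {11d} requires "blood pressure monitoring during the intravenous treatment (amiodarone or landiolol") and amiodarone could run longer than landiolol. The text does not support this. Intravenous amiodarone also stops when heart rate falls below 90, landiolol's 24 h bridging applies once its heart-rate target is met, and nothing says that monitoring ends with the infusion. Usual postoperative care continues. More hypotension from a longer infusion would in any case be a real consequence of the assigned strategy.

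**Conclusion.** The point holds for three secondary outcomes. Hemorrhagic and thromboembolic complications are counted from a time before randomisation, which dilutes the comparison. Hemodynamic intolerance is counted over a period that treatment may change, which biases the comparison if the drugs change ICU stay.

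The sizes are illustrations: a risk ratio of 2.40 reduced to between 1.99 and 1.43, with power down from 65% to between 56% and 34%, if 2 to 10% of patients have an earlier event; and a false nominal difference in about 19 to 48% of trials if ICU stay differs by one day (3 vs 4). Every rate and stay is assumed.

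A reader might conclude that all four event outcomes admit pre-treatment events, or that the surgery clock inflates the type I error. Neither follows: recurrence and drug-related adverse events cannot precede treatment, and pre-randomisation events are balanced in expectation. The primary outcome and sample size are untouched. The change is worth making but is not critical to the trial's main conclusion.

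**What to change.** In Objectives {7}, Table 1 and Outcomes {12}:

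1. Count hemorrhagic and thromboembolic complications from randomisation to 2 months and to 1 year.
2. Report ICU and hospital days from randomisation. This gains precision only.
3. Compare hemodynamic intolerance over one fixed window from randomisation, identical in both arms (for example 48 h), and report later events in the ICU separately.

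The cost is mainly one of definition. Later hypotension or bradycardia leaves the main comparison, which is why it should still be reported. Event times must be available in the eCRF; the article does not say that they are, so this needs checking first. Recruitment was still open at submission and no interim analysis is planned, so the definitions could be settled before any comparison by arm is made.
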